## Abstract

**Background**: Preoperative anxiety and postoperative pain are prevalent and are frequently associated with poor postoperative functional outcomes. Comprehensive postoperative management, including both pharmacological and psychological components, is essential for proper postoperative care and better recovery. While the analgesic effect of traditional non-pharmacological intervention, such as cognitive behavior therapy, has been investigated by other trial studies, the newer innovative methods for delivering psychological interventions for reducing anxiety and pain are extensively being investigated. Virtual reality (VR) has emerged as a novel and promising technology that offers opportunities to mitigate patient perception and cognitive responses, and has been shown to be associated with lower levels of anxiety and pain. The aim of this randomized clinical trial (RCT) is to determine whether delivering the psychological content through virtual reality (VR) along with the standard preoperative and postoperative care results in better anxiety and pain relief outcomes than standard care in patients undergoing spinal surgery. **Methods**: This study protocol outlines a parallel-group RCT to be conducted in the Department of Neurosurgery at the University Clinical Hospital of Medical University of Lodz. The objective is to assess the efficacy of immersive VR environments in reducing preoperative anxiety and postoperative pain intensity in the following day after surgery. Adult patients (18–70) will be randomly assigned to either (1) standard care before surgery (control group), (2) VR exposure simulating the hospital environment alongside standard care, or (3) VR-based exposure to calming natural landscapes accompanied by soothing background sound along with standard care. In each group, a minimum of 50 patients will be recruited. The primary outcome is the change in preoperative anxiety measured using the State-Trait Anxiety Inventory-State (STAI-S) scale from baseline to immediately after intervention. Secondary outcomes include postoperative pain measured using the Visual Analogue Scale (VAS), postoperative analgesic consumption, patient satisfaction, and VR-related adverse effects. To facilitate a comprehensive understanding of the VR intervention’s impact, the primary outcome will be complemented with measures of the adverse effects, level of immersion, and level of presence in the VR environment. Secondary outcomes of self-reported satisfaction scores and postoperative analgesics from patients’ medical charts will be assessed. **Conclusions**: This trial will evaluate whether VR-based interventions may reduce preoperative anxiety and postoperative pain in patients undergoing spine surgery. This study may provide evidence supporting the future implementation of VR as a non-pharmacological adjunct in perioperative care. This intervention may hold significant clinical relevance clinically, particularly in patients with high level of preoperative anxiety, by offering an alternative method to pharmacological anxiolytics in the future.

## 1. Background

Preoperative anxiety and stress are a frequently encountered phenomenon among patients, while such anxiety is experienced on different levels based on sociodemographic characteristics. The overall prevalence of preoperative anxiety varies and is reported in a range of 60–80% while other studies showed a wider range of 11–80% [1,2,3,4,5]. It occurs as a compatible and physiological response to surgical encounters and stress, which might occur anytime preoperatively [6]. The anxiety and stress are induced during hospitalization and intensified when a patient is informed about the need to undergo surgical intervention, and shortly before surgery [7].

Preoperative stress-related signs are associated with a potential change in patients’ psychological responses and hemodynamic parameters, including increased blood pressure and heart rate, that may pose a danger to the patients’ health [8]. Thus, these changes might affect the quality of anesthesia and demand for analgesics, postoperative pain, and possible delirium [9].

It also has significant impact on recovery, including longer postoperative hospital stay and even cognitive and behavioral ramifications. Thus, procedures which are painful lead to preoperative and postoperative anxiety, which causes fear in patients. This leads to a reduced pain threshold and higher postoperative pain and can affect patients’ compliance with subsequent future procedures [10]. A meta-analysis revealed that social support is crucial in reducing the postoperative anxiety among patients undergoing elective surgery. Conventional methods and interventions for managing pain and anxiety typically involve patient education and therapy with anti-anxiety medications prior to surgery to enhance patients’ comfort. However, randomized controlled trials have reported that these approaches provide only limited effectiveness and are associated with risks such as side effects, dependence, drug tolerance, and prolonged recovery time. As a result, there is increasing demand for non-pharmacological interventions to manage pain and anxiety, mitigating the drawbacks and risks associated with this traditional approach [11,12].

Research studies have shown that addressing pain through non-pharmacological intervention, such as cognitive behavioral therapy, music therapy, and interacting with immersive VR, results in a slower response to incoming pain signals [13]. Pain distractions such as television, music and games have been shown to have less of an effect on pain reduction than immersive VR exposure. Therefore, controlled preoperative anxiety and decreased pain reduce hospital stay lengths, healthcare costs, and postoperative complications. Pharmacological intervention is a current method used to reduce anxiety and pain preoperatively; however, it has been associated with a variety of risks which patients are facing, such as addiction, anaphylaxis, polypharmacy, and tolerance development [14]. The integration of non-pharmacological approaches has been one of the main priorities of healthcare reform in the last few years.

Current practice guidelines recommend that non-pharmacological interventions such as distraction and procedural preparation are routinely implemented in treatment plans. Distractions have been reported to have scientific validity as an effective non-pharmacologic intervention to reduce pain and anxiety in both pediatric and adult patients in clinical settings [15]. VR is considered to be an alternative type of non-pharmacologic anesthesia to modulate pain which helps with drawing attention and decreasing the amount of pain perceived [16]. Over the last few years, recent studies have assessed whether VR is suitable for the delivery of enhanced distractions and patient preoperative preparation interventions.

Studies have found that the decrease in pain experienced by the VR group is significantly less compared to the control group. Two systematic reviews have supported these findings; they studied the impact of VR on ninety-eight patients with hand injury undergoing dressing change.

Guo et al. (2015) [17] researched the effectiveness of virtual-reality-based distractions on pain among a group of patients with hand injuries during their dressing change. Ninety-eight patients were part of the control group and intervention group; the former scored better after the dressing change, and a statistical correlation between involvement and engagement in VR was found to significantly decrease pain.

Schwartz et al. (2020) [18] conducted a quality improvement VR project to not only reduce pain but also perioperative anxiety in pediatric burn patients. Forty-six children were given either VR or another distraction before undergoing their dressing change. Post-treatment scores were statistically more effective in the first group, with VR outperforming in each category.

Over the past five years, most of the research surrounding VR found it to be beneficial in clinical and surgical settings. Dehghan et al. (2019) researched the benefits of virtual reality on preoperative anxiety in children, where 40 children were allocated into two groups (control and intervention) [9]. The results indicated considerable changes for the intervention group from baseline to post-test, demonstrating that VR can substantially reduce anxiety in children in the preoperative setting. Sweta et al. (2019) studied the use of VR on patients following a dose of local anesthesia, gathering statistically significant improvements for preoperative and postoperative hemodynamic parameters and on the postoperative visual analog pain scale [19]. Findings from Moon et al. (2018) also highlighted how VR outperforms midazolam on patients’ and anesthesiologists’ satisfaction scores [20]. Therefore, three independent and systematic reviews have concluded that VR is effective at reducing acute and procedural pain through means of a distraction mechanism and may help to create an anxiolytic effect [21,22].

Therefore, the summarized findings suggest that immersive VR is a feasible and an alternative novel non-pharmacological method for reducing preoperative anxiety, improving and optimizing pain management. The results support its application and highlight its potential to enhance clinical outcomes across a variety of clinical settings.

Studies have reported that patients using anxiety reduction methods before surgery have less anxiety, lower pain, less demand for painkillers, and shorter hospital stays [16].

VR technology creates an immersive and multisensory environment that provides patients with modified experiences of reality and creates, as a result, a sense of “presence” in the virtual world.

In virtual environments, the patients experience similar physiological symptoms and anxiety as they do in real-life situations, thereby facilitating the habituation process. Thus, patients undergo a process of systemic desensitization through gradual exposure to an anxiety- or fear-inducing stimulus, with the ultimate goal of minimizing the patients’ intense and adverse behavior towards the stimulus through a series of systematic steps. In addition, psychoeducation can be used as a method to change the patients’ cognition about the stimulus to reinforce treatment benefits of systemic desensitization [23].

Moreover, the patients are given control of immersive, complex, and dynamic 360° videos in the virtual space where they are sensorially inserted and will interact with and navigate within the VR environment. This initiative allows patients to align their expectations with reality, as VR helps to diminish the gap between imagination and the real world [24,25]. However, there is not much research that measures the effects of VR on preoperative anxiety and pain reduction in correlation to the postoperative period and reported outcomes. Therefore, we planned the present project to evaluate the effect of VR on preoperative anxiety and pain and its impact postoperatively.

VR can provide clinical value through its application to adults undergoing outpatient procedures by offering a novel non-pharmacologic means to address common patient needs. This innovation can lead to optimal patient care, reduced costs, fewer pharmacological side effects and enhanced staff and patient experiences during outpatient procedures.

## 2. Pathomechanism of Pain and Anxiety

There is a strong correlation between anxiety and pain. To comprehend the mechanistic beginnings for VR analgesia, the neurobiological connectivity of the brain’s cortices and neurochemistry have been investigated, including the attentional, emotional, and cognitive processes [26].

Various receptors and proteins have been revealed to mediate pain attributed to periphery, as well as at the spinal cord level, where the gate control of pain transmission is located [27].

Nonetheless, anxiety has been researched mainly within the context of neuropsychology. Recent research on neuroimaging has revealed the brain’s inner network and how it mediates interactions of pain and anxiety. Both healthy participants and patients with emotional symptoms had key cortical areas actively involved in both conditions, including the anterior cingulate cortex (ACC), insular cortex (IC), and amygdala. Moreover, integrative neurobiological tools have allowed the central synapses to be investigated, as well as their potential involvement in anxiety disorders and chronic pain [27,28,29,30,31].

The human brain’s response to painful stimuli has been captured in functional imaging studies, with activity in the insula, anterior cingulate gyrus, the thalamus, and the primary somatosensory cortex and the periaqueductal gray matter. These regions host a network of circuitry that is involved from the top-down, bottom-up, and intercortical processing of such painful stimuli, and are the origins of where pain is perceived.

Other studies have shown that pre-LTP in the ACC may affect spinal nociceptive transmission via top-down ACC spinal facilitatory systems. ACC neurons in deeper layers are said to project to spinal cord dorsal horn neurons, and stimulating the ACC can lead to nociceptive responses. Such effects are then mediated by descending serotonergic projections from the rostral ventromedial medulla (RVM) [32]. The activation of these dorsal neurons, in turn, triggers the incoming pain-related somatosensory cortices and results in pain being experienced in a similar way that certain regions of the body experience pain. Therefore, the ACC–spinal network could hold the mechanism which underlies anxiety-triggered body pain. Through the activation of the ACC top-down modulation of the dorsal horn, abnormal activities stemming from fear or anxiousness can trigger neuronal activity in the spinal cord while interacting with the everyday ongoing sensory inputs from the periphery [33,34]. This would be enough of a stimulus for the pain-related areas of the cortex to activate, such as somatosensory cortex, ACC, and insular cortex, leading to a sensation of pain. Some activities may further improve top-down modulation via positive feedback.

NMDA receptors (NMDARs) play a significant role in pain associated with nerve injuries and peripheral tissues. Persistent activation of NMDARs can lead to increased sensitivity and responsiveness oof spinal cord neurons to such inputs, contributing to the central sensitization element of chronic pain [35]. Furthermore, NMDA-receptor-mediated postsynaptic LTP and kainate-receptor-mediated presynaptic LTP in the ACC are crucial for the perception of chronic pain and anxiety induced by physical harm [36,37]. It remains unclear if these synaptic regulation mechanisms also occur in other pain- or anxiety-related regions, as further research to investigate the modulatory mechanisms of the 5-HT system, at both the synaptic and molecular levels, is required [38].

However, these regions exhibit varying degrees of responses to aversive to non-aversive stimuli and a wide spectrum of task-based attention, distraction or affective conditions.

The responses observed by some subsets of these regions have been linked with a greater intensity of sensations and pain, as well as the unpleasantness of pain, as determined through imaging studies with well-controlled psychophysical measures. Despite this, challenges involving the separation of brain regions that process sensory information from those mediating the affective responses is still a controversial issue an area. Thus far, functional imaging or other investigative methods have failed to produce an objective, direct correlation of the pain experience, and have not clarified exactly how the brain’s sensory and affective mechanisms interact with one another to perceive pain as a reaction to potentially aversive stimuli.

Virtual reality has been proven to lessen pain, an effect known as “VR analgesia”. The subjective assessments of pain reduction through VR have been supported by functional MRI (fMRI) data, revealing decreased brain activity across regions typically highly active when exposed to experimental thermal pain stimulation [31]. Hoffman’s research, however, primarily focused on whether VR gaming, in its entirety, significantly diminishes increasing brain activities in the classic areas where pain is intrinsically linked with noxious thermal stimuli [39,40]. Another study compared the effects of VR to those of opioids on brain activities linked to thermal pain stimulation, and discovered that opioids and VR noticeably lessened pain-related brain activity in the insula and thalamus, but not in other areas of the pain circuitry.

Conversely, other cognitive activities have also been seen to reduce brain activity within the classic pain-processing circuitry during experimental pain stimulation. Valet et al. proposed that the cingulo–frontal cortex may apply top-down influences on periaqueductal gray matter and the posterior thalamus to lessen pain through distractions [41]. The heightened activity in the cingulo–frontal cortex might be a result of the increased cognitive load of such tasks and not of the mechanism of attention distraction itself [42]. Essentially, attention does not inherently require task loading; rather, task loading requires attention. Further research is needed to better understand these issues and to enhance our comprehension of the cortical processes responsible for pain modulation.

Despite there being studies reporting lower pain levels and increased comfort levels using VR glasses [43,44], little research has been conducted that specifically examines the overall impacts of virtual reality on anxiety in the context of neurosurgical and spinal surgery patients [45]. Therefore, this study aims to assess the effects of virtual reality applications on pain severity, anxiety level, and patient satisfaction in patients who undergo spinal surgery.

To the best of the authors’ knowledge, there is no previous study in the literature examining the impacts of virtual reality interventions when applied to three contrasting groups before neurosurgical or varying levels or types of spinal surgeries surrounding pain, anxiety, and vital signs. This study is being conducted to verify the effects of virtual reality intervention prior to spinal surgery on pain, anxiety, and vital signs.

## 3. Objectives

The aim of this research study is to evaluate the impact of immersive VR exposure on preoperative anxiety and pain, and, additionally, to assess whether VR intervention would significantly alleviate pain and anxiety levels of patients undergoing complex spinal surgeries. We hypothesize that the application of preoperative VR-based intervention will alleviate anxiety and pain both pre- and postoperatively when it is used as treatment to complement standard care compared to standard routine care alone, and that it may lead to better outcomes and higher satisfaction in patients. The primary objective is to evaluate whether procedural/educational VR reduces preoperative anxiety compared with standard care. Secondary objectives include comparing relaxation/distraction VR versus standard care, and procedural/educational VR versus relaxation/distraction VR with respect to postoperative pain, analgesic use, and patient satisfaction.

## 4. Material and Methods

### 4.1. Trial (Study) Design

This is a single-center study prospective, randomized, placebo-controlled trial with three parallel groups of adult patients (18 to 70 years) who have degenerative spinal disorders, specifically those diagnosed with lumbar or cervical spondylosis who are scheduled to undergo spinal fusion, discectomy, decompression, or stabilization procedures. Relevant surgical variables, including cervical/lumbar/thoracic location, type of surgery, surgical approach, duration of surgery, and perioperative complications, will be prospectively recorded and considered in adjusted analyses. The study assesses the influence of a single preoperative VR (exposure) session and its effect on both preoperative and postoperative anxiety and pain, as well as reported functional outcomes in patients undergoing elective spine surgery.

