### 4.5. Instruments and VR Utilization

The study affects all three groups, and the VR intervention includes only one session. All intervention sessions will be carried out individually. After these assessments, the patients will be oriented to the VR goggles and headset and given tutorials and instructions on how to use the device and how to remove it when they encounter potentially unwanted side effects such as dizziness, headache, nausea, or vomiting. In such cases, the procedure will be stopped and considered a withdrawal.

On the day before surgery, following baseline assessment and informed consent, the researcher will randomly allocate the patients to the VR group, control group, and VR relaxation/distraction group.

The study timeline will proceed as follows: enrollment and informed consent → baseline psychometric and pain assessments → randomization → VR or standard-care intervention on the day before surgery → immediate postintervention assessment → surgery → postoperative assessment within 24 h and analgesic assessment within 24–48 h postoperatively.

VR-related adverse effects, including dizziness, nausea, headache, cybersickness, and visual discomfort, will be prospectively recorded and analyzed descriptively throughout the intervention period.

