#### 4.7.4. Clinical Outcome Variables and Assessment

The primary outcome is the change in STAI-S score from baseline to immediately after intervention. Secondary outcomes include postoperative pain intensity assessed using the Visual Analogue Scale (VAS), postoperative analgesic use, patient satisfaction, and VR-related adverse effects. These outcomes will be measured preoperatively on the day before surgery, before the VR content exposure, and after. Measurements will be made again postoperatively—within 24 h. Preoperative and postoperative STAI-S and VAS will be compared for data analysis.

The baseline assessment is conducted one day before surgery, prior to the VR intervention, to capture the patient’s preoperative state under conditions closest to the actual surgical context. We believe this timing best reflects the anxiety and pain levels that the VR intervention aims to reduce. The postoperative assessment within 24 h is intended to evaluate the immediate effect of the intervention on perioperative anxiety and pain, which is the primary focus of our study. We acknowledge that longer-term outcomes may differ, but these are beyond the scope of the current trial, which specifically targets the short-term perioperative period (see Table 2).

The secondary outcome will be the patients’ quality of life and satisfaction (EVAN-G) of the VR intervention, time spent thinking about pain assessed, and postoperative analgesics measured from patient treatment charts within 24 and 48 h postoperatively and used for data analysis, as the level of satisfaction and thinking time spent on pain can contribute to an increased perception of pain.

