### 4.8. Data Collection

#### Baseline Value Measurement

On the day before surgery, after informed consent is obtained, evaluations, which include sociodemographic data and the psychometric questionnaires (STAI-S, PSS-10, BDI-II), pain score (VAS), and satisfaction (EVAN-G), will be collected by the researcher before the VR experience (see Table 3).

Perioperative anesthesia and analgesia management will follow standardized institutional protocols whenever feasible. Variables including anesthetic technique, intraoperative opioid administration, postoperative opioid consumption, rescue analgesic use, surgery duration, and perioperative complications will be prospectively recorded and considered in adjusted secondary analyses.

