### 4.9. Statistical Analysis

The statistical analysis will be performed under the mentorship of a biostatistician experienced in neurosurgical research. The nominal data will be presented as *n* (% of the total). The dependencies between them will be assessed using the test chosen based on the size of the smallest sample. All analyses will follow an intention-to-treat approach. The primary endpoint (change in STAI-S score from baseline to immediately postintervention) will be analyzed using one-way ANCOVA adjusted for baseline STAI-S. Pairwise comparisons will be Bonferroni-corrected. Secondary outcomes will be analyzed as follows: VAS pain at 24 h (ANCOVA adjusted for opioid dose), total opioid consumption (ANOVA or Kruskal–Wallis depending on distribution), patient satisfaction (Kruskal–Wallis), and rescue analgesic use (χ^2^ test). Longitudinal measures (baseline → post-VR → postoperative) will be evaluated with a linear mixed-effects model including group, time, and group × time interaction. Normality will be tested using the Shapiro–Wilk test. Missing data will be assessed for pattern and mechanism. Multiple imputation (m = 10) will be used if appropriate. Longitudinal analyses will primarily rely on linear mixed-effects models, which are robust to missing observations under missing-at-random assumptions. The primary comparison will evaluate procedural/educational VR versus standard care with respect to STAI-S score change. Secondary comparisons will include relaxation/distraction VR versus standard care and procedural/educational VR versus relaxation/distraction VR. Postoperative pain analyses will additionally be adjusted for perioperative opioid consumption and surgery duration when appropriate. Statistical analysis will be performed using STATISTICA 13.1 (TIBCO, Palo Alto, Santa Clara, CA, USA) and two-sided α = 0.05.

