## 5. Discussion

It is our understanding that there have not been any previous clinical trials or case studies conducted to determine the effects of VR-based interventions on preoperative pain and anxiety among neurosurgical patients. Preoperative anxiety has detrimental consequences as it raises postoperative complications, behavioral disorders, and can be disturbing emotionally.

Preoperative anxiety may occur due to multiple factors, such as former negative experiences, being exposed to terrifying stereotypes of doctors in the media, or even triggered by friends, family members, and colleagues [46]. Some common fears linked to preoperative anxiety are the fear of pain itself, blood injuries, and hospital settings. Milgrom et al. revealed four groups of anxiety-driven patients based on the origins/sources of the patients’ fear. Some were anxious due to specific surgical stimuli, distrust of hospital workers, general dental anxiety, and fear of the unknown. It was discovered that more invasive types of stimuli were more anxiety-provoking; however, stimuli linked to clinic offices, team members, and/or the equipment being used were the least fear-provoking. It was revealed that most of the patients felt anxious during their first clinical visit. Their main concerns were how anesthesia would be administrated, extraction, feelings of numbness, and the root canal treatment itself [47]. Recent research has connected anxiety with pain as it increases sympathetic activity, thereby releasing endogenous adrenaline and increased pain through nociceptors [48].

Chaves et al. surmised that there were no major differences between blood pressure (BP) and anxiety for either gender [49]. Conceição et al. found no statistically significant differences in heart rate (HR) and BP of anxious and non-anxious patients [50].

The purpose of this research is to further explore the beneficial impacts of VR on alleviating preoperative anxiety and levels of pain by examining three study groups. Prior reports have indicated that VR intervention can lessen the anxiety experienced by patients before surgery; however, other studies have found no such benefits among adult patients. Additionally, digital distraction techniques have been proven to lower stress and pain levels during interventions and painful procedures.

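### Perioperative complications arise after randomisation but are listed among the variables for adjusted analyses, which could distort the secondary comparisons of pain and analgesic use

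*Protocol article*

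**What the plan says.** Complications appear as a trial variable in two places. Section 4.1 groups them with spinal location, type of operation and approach as surgical variables and says that "duration of surgery, and perioperative complications, will be prospectively recorded and considered in adjusted analyses". Section 4.8 (Baseline Value Measurement) puts them beside anaesthetic and opioid variables: "surgery duration, and perioperative complications will be prospectively recorded and considered in adjusted secondary analyses".

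The rationale links them to what the intervention targets. The Background (section 1) says that "controlled preoperative anxiety and decreased pain reduce hospital stay lengths, healthcare costs, and postoperative complications". The Discussion (section 5) says: "Preoperative anxiety has detrimental consequences as it raises postoperative complications".

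The outcome list in section 4.7.4 does not contain them: "Secondary outcomes include postoperative pain intensity assessed using the Visual Analogue Scale (VAS), postoperative analgesic use, patient satisfaction, and VR-related adverse effects". The VR-related effects are defined in section 4.5 as symptoms such as dizziness and nausea, which "will be prospectively recorded and analyzed descriptively throughout the intervention period". Section 4.9 names a different set of covariates for pain: "Postoperative pain analyses will additionally be adjusted for perioperative opioid consumption and surgery duration when appropriate".

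**The concern.** A covariate in a randomised comparison should be fixed before randomisation, or at least be something that treatment cannot change. Complications meet neither condition. Listing them beside location and approach treats a possible result of treatment as if it were a baseline characteristic.

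Two things can go wrong in a model for postoperative pain or analgesic use. First, if VR lowers anxiety and thereby complications, as the rationale suggests, holding complications constant removes that part of the benefit. Second, complications and pain may share causes that are not in the model, such as a more difficult operation. Comparing arms at the same complication status then no longer compares randomised groups, and the bias can go in either direction.

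At stake is the interpretation of the secondary results on pain and analgesic use, not the primary result.

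**Working it through.** The article gives no figure on this point to reproduce, so the check has three parts: the order of events, a comparison of the covariate lists, and an illustration of size.

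**1. Order of events (section 4.5).** Baseline assessment, randomisation, VR or standard care on the day before surgery, immediate post-intervention assessment, surgery, postoperative assessment. The primary endpoint is complete before surgery begins. Perioperative complications, surgery duration and perioperative opioid use all come after allocation and after the VR session.

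**2. Covariate lists side by side.**

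| Variable | 4.1 | 4.8 | 4.9 | Can it be fixed before randomisation? |
|---|---|---|---|---|
| Location, type, approach | yes | no | no | yes, as planned |
| Anaesthetic technique | no | yes | no | yes, as planned |
| Surgery duration | yes | yes | yes (pain) | no |
| Opioid use | no | yes | yes (pain) | no |
| Rescue analgesic use | no | yes | no (an outcome) | no |
| Perioperative complications | yes | yes | no | no |

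The three sections do not give the same set. Section 4.9 commits to two post-randomisation covariates for pain and is silent on complications, while sections 4.1 and 4.8 keep complications available. Total opioid consumption is also a secondary outcome in section 4.9, so it is an outcome in one model and a covariate in another.

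**3. Size of the effect on the pain comparison (all inputs assumed).** In a linear model, the arm difference in pain is the direct effect plus g × (complication rate with VR − rate in controls), where g is the effect of one complication on VAS. Adjustment removes the second term. The article gives no complication rates, no value for g and no VAS range. A 0–100 scale is assumed here.

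| Control rate | VR rate | Removed if g = 10 | Removed if g = 20 |
|---|---|---|---|
| 10% | 5% | 10 × 0.05 = 0.5 | 20 × 0.05 = 1.0 |
| 20% | 10% | 10 × 0.10 = 1.0 | 20 × 0.10 = 2.0 |
| 30% | 15% | 10 × 0.15 = 1.5 | 20 × 0.15 = 3.0 |

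The loss is about 0.5 to 3 points. This covers only the first mechanism. The bias from shared causes cannot be sized from the article.

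**4. What a display by arm could show.** With 50 per arm (section 4.3.1), power to detect these differences at two-sided 0.05 is about 16%, 29% and 43% respectively, and 80% power would need about 435, 199 and 121 per arm. For 20% versus 10% the difference is 0.10, with SE = √(0.2 × 0.8/50 + 0.1 × 0.9/50) = √0.0050 = 0.071. The 95% interval is 0.10 ± 1.96 × 0.071, or about −4 to +24 percentage points. A descriptive table suits this precision; a formal test does not.

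**The case against.** The strongest reply is that the commitment is weak. Sections 4.1 and 4.8 say only that complications will be considered, section 4.9 does not name them as a covariate, and the primary analysis is untouched. All of this is correct and limits the weight of the point. It does not remove it: two sections give complications a role as an adjustment variable, and a later analysis plan would have to depart from both to correct it.

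A second reply is that the term is undefined and may include intraoperative events, whereas the rationale speaks of postoperative complications. That is fair, but intraoperative events also follow randomisation.

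A third reply is that complications are the least firmly committed of the post-randomisation covariates, since section 4.9 actually names opioid consumption and surgery duration. This stands, and the correction should cover those two as well.

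A reader might go further and infer that complications will never be reported by arm, or that a safety difference the trial expects will be adjusted away. The article supports neither. It is a condensed account, and a table of complications by arm may sit in the full protocol or analysis plan. The Objectives (section 3) state no hypothesis on complications; the links to anxiety are background. Using complications as a covariate leaves the counts by arm unchanged; what it can distort is the adjusted comparison of pain or analgesic use.

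**Conclusion.** The point holds in a limited form. Sections 4.1 and 4.8 place a post-randomisation event, which the article's own rationale connects to anxiety, among the variables for adjusted analyses. If it were used, the adjusted comparison of postoperative pain or analgesic use would no longer estimate the full effect of VR and could be biased. Under the assumed rates and pain effects, the part removed is about 0.5 to 3 points on a 0–100 scale. That is modest, rests entirely on assumptions, and leaves out bias from shared causes. The primary STAI-S result is not affected. On reporting, the article shows only that complications are not named as an outcome.

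**What to change.** - In sections 4.1 and 4.8, remove perioperative complications from the variables considered for adjustment in the main secondary models. If such an adjustment is wanted at all, make it a labelled sensitivity analysis.
- Keep surgical variables fixed before randomisation (location, planned type, approach) as covariates.
- State that complications will be described by randomised arm, with number and type, the arm difference and its confidence interval, and no formal test.
- In section 4.9, apply the same reasoning to opioid consumption and surgery duration: leave them out of the main pain model and, if wanted, show the adjusted result as a sensitivity analysis.
- Give one covariate list and make sections 4.1, 4.8 and 4.9 agree with it before unblinding.

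The cost is a few reworded sentences and one table from data already to be collected. It needs no additional patients, visits or measurements.
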